**2.4. Sample size calculation**

The proportion of pulmonary tuberculosis cases detected by Sidama tuberculosis control programme is about 20%.

n =

Where: n = the sample size

p = the proportion of pulmonary tuberculosis patients detected

q = 1- p

z = the percentage level at 95% confidence interval (1.96)

d = the margin of error = 5%

Based on this

n = = 246

**STUDY TWO - TO ESTIMATE THE TREATMENT OUTCOME OF TUBERCULOSIS PATIENTS SUPERVISED BY COMMUNITY HEALTH AGENTS/ TREATMENT SUPERVISORS**

**1. Objective**

- to estimate the treatment outcome of tuberculosis patients supervised by community health agents/ treatment supervisors

**2. Methods**

**2.1. Study design**

This is a randomized controlled community trial to estimate the tuberculosis treatment outcome through community based tuberculosis care. The investigator will select clusters from study districts. Based on the population, health service coverage and mainly on tuberculosis treatment outcome the investigator will match the clusters. He will match clusters and randomly assign them into intervention and non-intervention groups.

**Intervention sites**

The investigator, in collaboration with tuberculosis programme coordinators, will give training to health workers and community health agents about community based tuberculosis care and their role and responsibilities. The training will focus on tuberculosis case finding, case holding, drug management, recording and reporting as per the national guideline for community based tuberculosis prevention and control. The trainees will receive course materials and field guides to the trainees.

All diagnosed tuberculosis patients in the selected clusters will be included in the study. Health workers will inform tuberculosis patients about the disease and the selection criteria of treatment supervisors. Patients will select and come to health workers for discussion about treatment supervision. Once agreed upon, the health worker will discuss with treatment supervisor about community based tuberculosis care, their role and responsibility during the course of treatment.

Selection criteria for treatment supervisor selection is as follows: a volunteer leaving in the community who can read and write, can comprehend health education about tuberculosis prevention and control, has time to give daily dose as per the recommendation, can follow the patient through out the treatment duration and assist the patient during the follow up and drug collection. It is necessary that the treatment supervisors should have a known address so that supervisors from health facilities, Woreda, or investigator can contact during supervisory field visits in the course of patient management. Parents or guardians will supervise treatment of their children in paediatric age group less than 13 years if they can assume the role of treatment supervisor as per the selection criteria. If not, they will identify treatment supervisor.

Tuberculosis patients, who completed intensive phase in health facilities and patients on re-treatment regimen will not participate in the study. Treatment supervisors, who could not supervise at least the first two months of treatment, will be excluded.

Health workers will register tuberculosis patients on programme and research formats prepared for community based tuberculosis care. Tuberculosis treatment supervisors will also register the patients on the daily treatment follow up format. Health workers will record tuberculosis case finding and treatment outcome of the intervention sites. They will submit research formats to the investigator and will keep copies of their health institutions.

The regional tuberculosis control programme will supply all the needed drug and supplies to the respective districts and facilities via existing health care system. The scheme of supervision will have the following pattern: tuberculosis treatment supervisors will supervise tuberculosis patients. Health extension workers will supervise tuberculosis treatment supervisors. Health workers will supervise both activities. The investigator and coordinators at all levels - regional, zonal, and district will supervise health facilities, health extension workers, tuberculosis treatment supervisors and the patients as the regional supervision scheme.

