**Study - II**

This is a randomized controlled community trial to estimate the treatment outcome of tuberculosis patients treated by community based directly observed short course therapy. The investigator will select clusters and match for tuberculosis treatment outcome. Then will randomly allocate them to intervention and control clusters. Health workers and community health agents in the intervention clusters will receive training on community-based tuberculosis care and its implementation. They will also discuss with diagnosed tuberculosis patients about the disease and selection of treatment supervisor. Tuberculosis patients will select tuberculosis treatment supervisor from their area and discuss with health worker about their role and responsibility. Once agreed up on, tuberculosis patients will start supervised short course therapy in their community under tuberculosis treatment supervisor. The study will follow the national tuberculosis programme guideline for patient diagnosis, treatment, follow-up, recording and reporting. Patients in the non-intervention clusters will continue conventional health-facility based directly observed short course therapy.

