**Non-intervention sites**

Tuberculosis patients in the non-intervention district will follow the existing facility based tuberculosis case finding and treatment. They will receive supplies and programme managers will carry out supervision according to the existing supervision system.

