**Patient follow up and treatment outcome**

1. Disease classification PTB+ve ______ PTB -ve ______ EPTB ________

2. Patient category New____ Relapse____ Failure_____ Defaulter______

Transfer in____ other (specify) _________________

3. Sputum smear results of PTB +ve patients

2nd month __________ 5th month _________ 7th month _______

4. Treatment outcome cured ___ treatment completed ___ died ______

Defaulted ____ failure ____ transfer out _______

Other (specify) ___________________________

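### Study Two states its exclusions only for the intervention sites, so the text permits patients to be removed from one arm after clusters are randomised

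*Protocol*

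**What the plan says.** The relevant text is in the Protocol, Study Two, section 2.1 (Study design).

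- **Allocation.** Clusters are the unit: "He will match clusters and randomly assign them into intervention and non-intervention groups". Patients are diagnosed and supervisors chosen afterwards.
- **Intervention sites, inclusion.** "All diagnosed tuberculosis patients in the selected clusters will be included in the study".
- **Intervention sites, patient exclusions.** "Tuberculosis patients, who completed intensive phase in health facilities and patients on re-treatment regimen will not participate in the study".
- **Intervention sites, supervisor exclusion.** "Treatment supervisors, who could not supervise at least the first two months of treatment, will be excluded".
- **Non-intervention sites.** "Tuberculosis patients in the non-intervention district will follow the existing facility based tuberculosis case finding and treatment". No inclusion or exclusion rule follows. Section 6.2 (Study - II) says of the same arm: "Patients in the non-intervention clusters will continue conventional health-facility based directly observed short course therapy".

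The treatment outcome questionnaire has a patient category field that offers relapse, failure and defaulter as well as new cases.

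**The concern.** In a cluster-randomised trial the arms stay comparable only if the same rule decides, in both, which patients are counted. Here the rules stand under one arm's heading and act after allocation.

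The two-month rule is the most sensitive. Supervision may end early because the supervisor withdrew, but it may also end because the patient died, defaulted or moved away. If the patient leaves the count with the supervisor, some early failures disappear from the intervention denominator while similar failures in control clusters remain. The difference in success rates could then exceed the true effect.

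The inclusion of all diagnosed patients and the exclusions also stand in the same subsection without being reconciled.

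**Working it through.** **1. Can each rule operate in both arms?**

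| Rule | Intervention clusters | Control clusters |
|---|---|---|
| Intensive phase completed in a facility | Stated | Not stated. Control treatment is facility-based, so if applied during follow-up it would remove every control patient who got through that phase. It can apply only if fixed at entry. |
| Re-treatment regimen | Stated | Not stated. Could be read as study-wide. |
| Supervisor not lasting two months | Stated | No community supervisor, so no counterpart. |

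**2. The plan's own figures** (Study Two, section 2.4: 70% versus 85%, z values 1.96 and 1.28, ICC 0.04, cluster size 15).

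- (1.96 + 1.28)² × 2 × 0.775 × 0.225 / 0.15² = 162.7, so 163 per group.
- Design effect 1 + 14 × 0.04 = 1.56. Then 1.56 × 163 = 254.3, so 255, and 255 / 15 = 17 clusters per group.

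These reproduce. The point rests on wording, not on an arithmetic error.

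**3. Effect if patients are dropped with their supervisors.** Let f be the share of intervention patients dropped and s their true success rate. The documents give neither, so both are assumptions. With no true effect and 70% success in both arms:

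observed intervention success = (0.70 − f × s) / (1 − f)

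The type I error is that of a two-sided 5% two-proportion z-test. The effective size is 255 / 1.56 = 163 per arm, reduced by the fraction f in the intervention arm.

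| f | s | Calculation | Observed | Bias (points) | Type I error |
|---|---|---|---|---|---|
| 5% | 50% | (0.70 − 0.025) / 0.95 | 71.1% | +1.1 | 5.5% |
| 5% | 0% | 0.70 / 0.95 | 73.7% | +3.7 | 11% |
| 10% | 50% | (0.70 − 0.05) / 0.90 | 72.2% | +2.2 | 7% |
| 10% | 0% | 0.70 / 0.90 | 77.8% | +7.8 | 34% |
| any | 70% | (0.70 − 0.70f) / (1 − f) | 70.0% | 0 | 5% |

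If the patients are kept, f = 0 and the bias is zero.

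**4. Re-treatment exclusion in one arm only.** If 10% of patients are re-treatment cases with 50% success (assumed), the same formula gives (0.70 − 0.05) / 0.90 = 72.2%, or +2.2 points.

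**5. Intensive-phase exclusion in one arm only.** These patients have already come through the early phase. If 10% are dropped and 90% of them would succeed (assumed), the result is (0.70 − 0.09) / 0.90 = 67.8%, or −2.2 points.

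**The case against.** The strongest reply is that the two-month sentence excludes supervisors, not patients. The same subsection lists suitability criteria for supervisors and provides for another one where a parent or guardian does not qualify. Health workers, not supervisors, register patients and record outcomes, so outcome data survive a change of supervisor. This stands: a reader might infer that patients are dropped, but the protocol does not say so. A purely up-front reading is nevertheless strained. The selection criteria already require someone able to stay with the patient for the whole course, so a two-month entry criterion would be weaker and redundant. The sentence also follows the patient exclusions rather than standing among the criteria.

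Second, the patient exclusions speak of not participating in the study, which could cover both arms. The inclusion rule sits under the same heading, so the heading alone is weak evidence of scope. This also stands in part. One-arm removal of re-treatment patients is an inference, and the category field on the outcome form does not settle it, because that field is also needed to apply an exclusion. The gap remains, since the control text adopts none of these rules.

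Third, a reader might conclude that the bias always favours the intervention. The documents do not support that: step 5 of the working runs the other way, and the bias vanishes under the conditions in step 3.

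Fourth, analysis populations often belong in a SAP. That is true of the detail, but these are exclusion rules that the protocol itself states, and stated for one arm.

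**Conclusion.** The concern holds in a limited form. The protocol permits arm-specific exclusion after cluster randomisation; it does not establish that this will happen. Confidence is high that the text is asymmetric and moderate that the two-month rule refers to an event during treatment.

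If patients leave with their supervisors, the overstatement is about 1 to 8 points for the assumed ranges in step 3, with a type I error of about 5.5% to 34% instead of 5%. The planned difference is 15 points. Because the exclusions can pull in opposite directions, the net sign is not certain. To say that the randomised comparison is broken, or that intervention success is inflated, would go beyond the text. This should be corrected, but it is not a defect that invalidates the design.

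**What to change.** 1. Reconcile the Intervention sites and Non-intervention sites text into one patient eligibility rule, applied at registration in both arms. The re-treatment and prior intensive-phase exclusions should be part of it, with the latter fixed at entry so that it can apply to facility-treated controls.
2. State that the two-month criterion concerns the selection of supervisors only and removes no patient from the study. Reconcile it with the selection criterion that covers the whole course of treatment.
3. Count every eligible registered patient in the allocated cluster, whatever happens to the supervisor. An analysis of supervised patients only can be secondary.

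The cost is protocol wording, plus applying the same eligibility check to control registrations. Treatment and supervision of patients need not change. The intervention success rate may look less favourable than it would with supervised patients alone.

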**Study - III**

This is a randomized controlled community trial to find out the cost per tuberculosis patient treated successfully. The study follows societal perspective of cost analysis. The main cost items related to the costs of tuberculosis prevention and control programme will be collected as for diagnosis, follow up and supervision including patient and community health workers time and costs. Data collectors will also get records from district finance offices. The data collectors will calculate cost of time based on monthly salary of health workers and tuberculosis patients if they are in the productive age groups. In addition, the cost of the person accompanying the patient will be included. The outcome indicator for the study is the cost per patient treated successfully.

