**2. Methods**

**2.1. Study design**

This is a randomized controlled community trial to find out the costs per tuberculosis patient treated successfully in the intervention and non-intervention districts. Cost related to tuberculosis control programme in the study sites will be determined according to the actual expenses and time cost. Programme coordinators, health workers, community health agents, tuberculosis treatment supervisors, tuberculosis patients and relatives accompanying them to health facilities in the study sites will be included in the study.

The cost analysis will follow societal perspective to analyse the cost per patient. The data collectors will obtain financial reports from districts and health institutions finance sections to collect expenditures for tuberculosis control programme, health workers and community health agents’ time and costs associated to tuberculosis prevention and control activities. In addition, they will collect cost of the patient and the relative who accompanied them during their visit to health institutions.

The investigator will use cost per tuberculosis patient successfully treated as an outcome measure. Future cost and productivity gains will not be included in the study. Standard cost estimation of all expenses and time of the patient, treatment supervisor and health workers will be done. Data collectors will use a structured pre-tested questionnaire for data collection.

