**Cost items for daily dose of intensive phase treatment**

1. number of hours taken for explaining about the disease to the patient _
2. number of hours taken for daily dose supervision and registration _____

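### The clinic health-worker cost form has no item for briefing treatment supervisors or for supervising them and the extension workers, so this part of the intervention arm's cost would be under-recorded

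*Protocol*

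**What the plan says.** Under Intervention sites (Protocol, Study Two, 2.1), the patient chooses a treatment supervisor and discusses the choice at the clinic: "Patients will select and come to health workers for discussion about treatment supervision". The supervisor is then instructed: "the health worker will discuss with treatment supervisor about community based tuberculosis care, their role and responsibility during the course of treatment". The supervision scheme has three layers. Treatment supervisors watch patients, extension workers watch treatment supervisors, and then "Health workers will supervise both activities". The same section requires supervisors to have a known address so that, among others, staff from health facilities can find them on field visits.

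The control arm has none of this work: "Tuberculosis patients in the non-intervention district will follow the existing facility based tuberculosis case finding and treatment".

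Study Three, 2.1 takes a societal perspective and makes this commitment: "Standard cost estimation of all expenses and time of the patient, treatment supervisor and health workers will be done". Study Three, 2.2 adds costs of supervision and of monitoring and evaluation. Section 6.2, Study III, says how time is priced: "The data collectors will calculate cost of time based on monthly salary of health workers".

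The annexed TB OPD form has four time items. Two are for explaining the disease, one in each treatment phase. One is for the intensive phase: "number of hours taken for daily dose supervision and registration". The last is for drug administration and registration in the continuation phase.

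**The concern.** Pricing time from salary requires hours. The clinic form collects hours for work that facility-based care uses heavily, daily dose observation above all. It has no line for the clinic work that community care adds in its place. The unrecorded tasks exist in one arm only, so the omission does not cancel in the comparison.

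Cost per patient successfully treated is Study III's outcome measure. A component missing from one arm's numerator lowers that arm's figure. Later analysis cannot restore hours that were never collected, so the form itself needs attention.

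**Working it through.** The protocol gives no figure for these hours, so the main check sets tasks against forms. The Study III sample size (123, inflated to 192) plays no part.

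**Who is meant by health workers.** The Intervention sites text names extension workers separately from health workers, has patients come to the health workers, and has health workers keep copies for their own institutions. That points to clinic staff.

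**Clinic tasks added by the intervention, and where each is timed:**

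| Task | TB OPD form (clinic) | Community health worker form | District form |
| --- | --- | --- | --- |
| Agreeing the choice of supervisor with the patient | No own item; may partly fall under explaining the disease | Yes, with the sputum-result talk | No |
| Briefing the supervisor | No item | Yes | No |
| Supervising treatment supervisors and extension workers | No item | Supervision hours and days | Visits, hours per visit, staff covered |
| Travel for that supervision | No item | Travel expense line in the treatment block | Kilometres and fuel |

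The laboratory technician form covers sputum work only. Two tasks therefore have no place at clinic level: briefing the supervisor, and supervision with its travel. The selection talk is only partly covered.

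**Could accounts replace the form?** Finance reports are to be used, and the district form lists staff with monthly salaries. No rule is given for splitting salaries by task or by arm. Section 6.1 counts 1 hospital, 20 health centres and 26 health stations, which gives 1 + 20 + 26 = 47 facilities delivering DOTS for about 2.8 million people. 2,800,000 / 47 is about 60,000 people per facility. Study Two, 2.4 ends with clusters of about 12,000 people, and 60,000 / 12,000 = 5 cluster-sized populations. An average facility's accounts could therefore mix arms. The protocol does not say which facility serves which cluster.

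**Illustration of size. Every input is an assumption except where marked:**

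Unrecorded hours per intervention patient = briefing hours + (supervision hours per month × months of treatment). The 6 to 8 months is the follow-up for treatment outcome in Study Two, 2.4.

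- Low: 0.5 + 0.25 × 6 = 2.0 h
- Middle: 1 + 0.5 × 6 = 4.0 h
- High: 2 + 1 × 8 = 10.0 h

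Per success, at the 85% success that Study Two assumes for the intervention arm: 2.0 / 0.85 = 2.4 h, 4.0 / 0.85 = 4.7 h, 10.0 / 0.85 = 11.8 h. The same tasks take 0 h in control. If one supervisory visit covers several patients, the supervision term is divided among them. The protocol gives no wage, so none of this converts to money.

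**The case against.** - **Existing items may absorb part of the work.** The protocol describes one conversation covering both the disease and the criteria for choosing a supervisor, and drug handover can sit under drug administration. This stands. It does not reach the briefing of a third person or supervision in the field.
- **Community staff may do much of it.** Study Four, 2.1 uses the term health workers broadly enough to include extension workers and community health agents, and the community health worker form times closely matching tasks. This stands in part: time those staff spend is recorded, and the clinic's share may be small. The Study Two text still assigns briefing and supervision to health workers named apart from extension workers.
- **The costs are in scope.** Study Three includes supervision costs, costs of coordinators in the district and health institution, and finance reports. True, and nothing shows that these sources exclude the cost. Scope is not measurement, however, and no rule recovers the hours.
- **A reader might infer that community care will look cheaper overall than it is.** The documents do not support that. The patient form itemises accompanying relatives' costs for diagnosis but not for treatment visits, although Study Three promises them. Daily facility visits would plausibly incur more of those costs, so this gap may run the other way.
- **A reader might also infer that much of the saving in staff time is an artefact.** If daily observation took an assumed 10 to 15 minutes for about 60 doses, control patients would generate 10 to 15 hours. The 2 to 10 hours above would then be between 2/15 = 13% and 10/10 = 100% of that. The range pairs extremes of invented inputs and ignores shared visits. It concerns staff hours only, which are one part of a societal cost, and it carries no evidential weight.

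**Conclusion.** The point holds as a gap in one form. Clinic-level briefing of treatment supervisors, and clinic-level supervision of them and of the extension workers with its travel, are required in the intervention arm and fall within what Study III undertakes to cost. They have no line on the only time form for tuberculosis-clinic staff. Taken alone, the gap lowers the intervention arm's recorded cost and so favours community care.

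This rests on two readings: that health workers in the Intervention sites text means clinic staff, and that the form is used as printed. The size is unknown and may be modest. The net direction for total cost per success is not established. This is a cheap improvement and does not undermine the study.

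**What to change.** Add to the TB OPD form, before data collection:

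1. Hours spent agreeing the choice of treatment supervisor with the patient and briefing the supervisor, kept separate from explaining the disease.
2. For supervision of treatment supervisors and of extension workers: hours, number of visits, travel expense and number of patients covered.

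Value the time at the health worker's salary, as for the existing items, and include it in the intervention arm's cost. State that time already entered on the community health worker form is not counted again. Recording patients covered allows a shared visit to be divided among them.

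The cost is a few extra lines and slightly more data collection. The stated cost advantage of community care may shrink.
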